### 2.4 Intervention

Participants will receive an intravenous infusion of AA or the matching placebo (saline) immediately prior to anesthesia induction for each MECT session. This administration is fully synchronized with the MECT procedure, meaning that each intervention (or placebo) dose is given before every electroconvulsive therapy session. Participants in the AA Group will receive 500 mg of AA (2 mL containing 0.5 g; Xinhua Pharmaceutical Co., Ltd., Zibo, Shandong, China),constituted by diluting the solution with normal saline to a final volume of 100 mL. Participants in the Placebo Group will receive 100 mL of normal saline alone. All study solutions will be prepared under aseptic conditions by independent personnel not involved in the trial’s clinical conduct. The final solutions for both groups are visually indistinguishable (clear and colorless liquids) and will be dispensed in identical, tamper-evident, light-proof containers to ensure blinding throughout preparation, handling, and administration.

### 2.5 MECT Procedure

The MECT protocol is determined by the treating psychiatrist, initiated with up to four weekly sessions during the first treatment week before transitioning to a maintenance schedule of three sessions per week. The procedure utilizes a Thymatron DGx device (Somatics, LLC, Lake Bluff, IL, USA) with bitemporal electrode placement positioned 5 cm superior to the lateral orbital rim. Stimulation parameters consist of square-wave stimulation at 900 mA, with 125 bidirectional pulses per second and a brief-pulse width of 1.5 ms [33]. The initial electrical charge is calculated using the half-age method, with subsequent doses adjusted in 5% increments per session based on continuous electroencephalography (EEG) monitoring of seizure characteristics including morphology and duration. Anesthetic administration includes intravenous atropine (0.5 mg), propofol (2 mg/kg), and succinylcholine (1 mg/kg), with dosage customization according to individual patient response to achieve optimal seizure expression. The electrical stimulus will be delivered immediately following the cessation of succinylcholine-induced fasciculations, under conditions of adequate oxygenation. Treatment efficacy is confirmed through electrographic seizure duration exceeding 25 seconds [34,35] and characteristic EEG patterns demonstrating polyspike-wave complexes, 3-Hz spike-and-wave discharges, and postictal suppression [33,34,36].

### 2.6 Outcomes

Outcome categories and their assessment timepoints are detailed in Table 1. Data will be collected by independent investigators who are blind to group allocation and intervention assignments.

**Table 1. T001:** **Outcome measurements**.

Outcomes	Measurements	Scheduled time		
		Baseline	Each MECT	Before discharge
Primary outcome:				
Treatment response rate	HAMD-24 scale	×		×
Secondary outcomes:				
Depression remission rate	HAMD-24 scale	×		×
Suicide ideation remission rate	HAMD-24 scale (item 3)	×		×
Associated psychotic symptoms	BPRS scale	×		×
Cognition	MoCA scale	×		×
Electroconvulsive parameters	Field recording		×	
Anesthesia related data	Field recording		×	
Blood biomarkers	Blood detection	×		×
Safety outcomes:				
Adverse effects of ascorbic acid	Observation and inquiry		×	×
Adverse effects of MECT	Observation and inquiry		×	×

BPRS, Brief Psychiatric Rating Scale; HAMD-24, 224-item Hamilton Depression Rating Scale; MECT, modified electroconvulsive therapy; MoCA, Montreal Cognitive Assessment; "×" symbol indicates the time point at which each assessment is carried out.

For the confirmatory index, the primary outcome is the treatment response rate of the group. Response is operationally defined as achieving at least a 50% reduction from baseline on the HAMD-24 total score by the end of treatment [37]. A qualified psychiatrist rates the 24 items of the HAMD-24 on a 0–4 severity scale (0 = none, 1 = mild, 2 = moderate, 3 = severe, 4 = very severe) of 24 items [37]. Treatment response rate is expressed as the percentage of patients responding to MECT relative to the total number of patients in each group. The rationale for selecting the “response rate” as the primary outcome is as follows: (1) the response to an antidepressant treatment with a ≥50% reduction in the scale score has been generally recognized as a clinically meaningful treatment success intuitively reflecting the efficacy intensity of the intervention measures in confirmatory studies [38,39]; and (2) is an internationally accepted consensus standard for antidepressant efficacy evaluation by the US Food and Drug Administration (FDA) and European Medicines Agency (EMA) [40,41], and has been widely used as the primary outcome in evaluating the efficacy of MECT as well [42,43].

Secondary outcomes are as follows. The rate of remission of depression after MECT treatment is assessed with the HAMD-24 scale. Remission requires HAMD-24 score <10 after two sequential sessions, and the rate is derived from the number of remitters divided by the total participants per group [44]. For suicidal ideation (SI), defined as a score ≥2 on HAMD-24 item 3, the remission rate represents the proportion of baseline SI-positive patients achieving a score <2 after MECT [45]. Assessment of accompanying psychotic symptoms will be done with the 18-item Brief Psychiatric Rating Scale (BPRS), which uses a 7-point scale per item. The total score (18 to 126) serves as an indicator of severity; higher values indicate worse symptoms [46]. The Montreal Cognitive Assessment (MoCA) serves to rapidly assess cognitive function, providing a total score of 30; better function is indicated by higher scores [47]. Parameters recorded post-stimulation include: 3 Hz spike and wave activity; multiple spike activity; post-seizure suppression; and seizure duration. Based on common practice in MECT trials, a seizure with a duration longer than 25 s is considered indicative of an effective treatment [33,34], and seizure quality on EEG will be assessed with a specific standardized scale. Vital signs (oxygen saturation, heart rate, blood pressure, etc.), and anesthetic indices (duration, dosages of anesthetics) during each MECT treatment will be recorded. Blood samples will be collected to assess potential mechanistic biomarkers including AA, interleukin-1β (IL-1β), IL-6, tumor necrosis factor alpha (TNF-α), and BDNF.

Safety outcomes will be monitored as well, focusing on adverse events (AEs) associated with AA and/or MECT. An AE constitutes any unforeseen medical occurrence after the intervention. Although AA is generally well-tolerated, any newly observed side effects will be recorded, as well as those of MECT, including memory deficits and muscle pain. Participants will be instructed to report any AEs, which will be assessed by a physician and documented. The occurrence of a serious AE will trigger unblinding, administration of necessary treatment, and mandatory reporting to the Institutional Review Board.

### 2.7 Sample-Size Estimation

The primary outcome is the response rate of the group to MECT. As no prior data exist regarding the efficacy of AA augmentation in individuals diagnosed with major depressive disorder receiving MECT, the required sample size was determined based on our pilot study (*n *= 40, i.e., 20/gp) conducted over 6 mo, which indicated a response rate of 60% (12/20) in the placebo group and an improvement of 20% (16/20) in the AA group. With a two-sided α of 0.05, a power of 85% (1-β = 0.85), and 1:1 allocation, the calculation performed with PASS software (version 2021, NCSS, LLC, Kaysville, UT, USA) indicated a requirement of 93 participants/gp. To allow for an anticipated 22.5% attrition rate, a target enrollment of 120 participants/gp is planned, resulting in a final total sample of 240 subjects.

### 2.8 Statistical Analysis

The intention-to-treat (ITT) analysis set in this study will include all randomly assigned participants, regardless of whether they received MECT treatment or completed the follow-up assessments. Analyses will be conducted using SPSS (version 26, IBM Corp., Armonk, NY, USA). Missing outcome or covariate data, including those from participants in the ITT set without post-baseline data, will be handled using multiple imputation, and a mixed model for repeated measures (MMRM) will be used where appropriate. For the primary outcome (the rate of response to MECT), binary logistic regression, with treatment group as the independent variable and pre-specified stratification factors included as covariates, will serve as the primary analytical method, and results will include an adjusted odds ratio (aOR) with a 95% confidence interval. Additionally, potential interaction effects between the stratification factors (age, sex, baseline HAMD-24 score) and the treatment group will be explored within this model for the primary outcome. The Chi-square test will be used as a supplementary analysis. Categorical variables, expressed as counts (percentages), will be compared between groups using the Chi-square test (or the Fisher’s exact test). Continuous variables will be presented as mean (standard deviation) (if normally distributed) or median (interquartile range) (if non-normally distributed), and compared using *t*-test or nonparametric tests (e.g., Mann-Whitney U test), as appropriate. For secondary-outcome analyses, logistic regression will be performed to adjust for potential confounders. For multiple comparisons, the Bonferroni correction will be applied for the secondary and exploratory outcomes. Specifically, the Bonferroni correction will be applied uniformly across all pre-specified secondary outcomes to control the family-wise error rate. We acknowledge that this is a conservative approach, which prioritizes the control of Type I error over statistical power for these outcomes. Given their exploratory feature, between-group differences in blood biomarker levels from baseline to post-treatment will be compared using an analysis of covariance (ANCOVA) adjusted for baseline values, and the Benjamini–Hochberg false discovery rate (FDR) procedure will be applied to correct for multiple testing. Pre-specified subgroup analyses will be conducted based on age (<45 and ≥45 years), sex (male and female), and baseline HAMD-24 score (divided at the median). These analyses will be performed by including an interaction term between the treatment group and the subgroup variable in the primary statistical model (binary logistic regression). Given the exploratory and hypothesis-generating nature of these subgroup analyses, no multiplicity adjustment will be applied to the interaction tests, and the results will be interpreted with caution. Sensitivity analyses will include the per-protocol (PP) analysis and complete-case analysis, an evaluation using alternative missing-data-handling strategies, and re-analyses excluding specific populations (e.g., protocol violators) to assess the robustness of the findings. All hypothesis tests will be two-tailed, and a statistical significance level will be set at* p *< 0.05.

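### BPRS and MoCA totals are left to unadjusted two-sample tests although their baselines are collected; baseline-adjusted ANCOVA is planned only for the blood biomarkers

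*Protocol article*

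**What the plan says.** All references are to the protocol article.

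- **Outcome type (2.6 Outcomes).** For the BPRS, "The total score (18 to 126) serves as an indicator of severity". The MoCA is likewise a total score, with a maximum of 30. Table 1 schedules both at baseline and before discharge.
- **Default test (2.8 Statistical Analysis).** Continuous variables are compared by t-test or "nonparametric tests (e.g., Mann-Whitney U test), as appropriate". The text does not say whether the end score or the change from baseline is compared.
- **Adjusted model for secondary outcomes (2.8).** "For secondary-outcome analyses, logistic regression will be performed to adjust for potential confounders". The confounders are not named.
- **Baseline-adjusted model (2.8).** ANCOVA with the baseline value is specified for the blood biomarkers only.
- **Repeated measures (2.8).** In the sentence on missing data, "a mixed model for repeated measures (MMRM) will be used where appropriate". No outcome is attached to it.
- **Per-session data (2.6, Table 1).** The row "Electroconvulsive parameters" and the row for anaesthesia data are recorded at each MECT session and have no baseline entry.
- **Multiplicity (2.8).** Bonferroni is applied across all secondary outcomes, and the cost in power is acknowledged.

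**The concern.** Logistic regression needs a binary outcome. The BPRS and MoCA totals would have to be dichotomised to use it, and no cut-off is given. Once it is set aside, the named methods for these two scales are an unadjusted t-test or Mann-Whitney test. The baseline values are therefore collected but enter no stated model for these scales, while the biomarkers, which the same section calls exploratory, get the more efficient method.

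Precision is at stake, not validity. The Introduction hypothesises that ascorbic acid may ease the adverse effects of MECT, and it gives cognitive impairment as an example of those effects. The MoCA is the scheduled cognitive scale. Its comparison already pays for a Bonferroni correction, so discarding baseline information as well is an avoidable loss.

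**Working it through.** **1. The plan's own figure.** Inputs from 2.7: "With a two-sided α of 0.05, a power of 85% (1-β = 0.85), and 1:1 allocation"; "a response rate of 60% (12/20) in the placebo group"; "an improvement of 20% (16/20) in the AA group". With p₁ = 0.6, p₂ = 0.8 and mean 0.7:

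n = [1.96·√(2·0.7·0.3) + 1.036·√(0.24 + 0.16)]² / 0.2² = 92.7, so 93 per group.

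Allowing for attrition, 93 / (1 − 0.225) = 120. Both stated figures reproduce. They concern the binary primary outcome and do not depend on this point.

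**2. Assumptions for BPRS and MoCA.** The document gives no standard deviation, target difference or correlation for either scale. I assume a standardised difference d = 0.4 and a baseline-to-end correlation r of 0.3 to 0.7. From the document I take n = 93 evaluable per group and α = 0.05/7, since Table 1 lists seven secondary rows.

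**3. Formula.** Relative to a test on the end score, ANCOVA multiplies the variance by v = 1 − r². A change-score test multiplies it by v = 2(1 − r). Then

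power = Φ( d·√(n/2) / √v − z ), with d·√(n/2) = 0.4·√46.5 = 2.728 and z = 2.690 for α = 0.05/7.

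**4. Results at 93 per group, α = 0.05/7.**

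| Analysis | r = 0.3 | r = 0.5 | r = 0.7 |
|---|---|---|---|
| End score, unadjusted (v = 1) | 51.5% | 51.5% | 51.5% |
| Change score, v | 1.4 | 1.0 | 0.6 |
| Change score, power | 35.0% | 51.5% | 79.7% |
| ANCOVA, v | 0.91 | 0.75 | 0.51 |
| ANCOVA, power | 56.7% | 67.7% | 87.1% |

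For example, at r = 0.5: 2.728/√0.75 − 2.690 = 0.459, and Φ(0.459) = 67.7%.

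**5. Sensitivity.**
- With all 120 per group, the end-score test has 65.8% power and ANCOVA has 71.2%, 81.3% or 95.0%.
- With α = 0.05/6 (biomarkers left out, since they have their own false discovery rate procedure) and 93 per group: 53.6% against 58.7%, 69.5% or 88.1%.
- With α = 0.05 and 93 per group: 77.9% against 81.6%, 88.3% or 96.9%.

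**6. ANCOVA against a change-score test.** The variance ratio is (1 − r²)/(2(1 − r)) = (1 + r)/2, that is 0.65, 0.75 or 0.85. ANCOVA is never less efficient. If the planned t-test is on change scores, the gain is smaller than in the end-score comparison when r exceeds 0.5, the same at 0.5, and larger below 0.5.

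**The case against.** **A condensed article need not assign a model to every outcome.** This is fair, and it disposes of any complaint that detail is missing. It does not dispose of what the article does fix: a default test for continuous variables, a single adjusted model for secondary outcomes that does not suit two of them, and ANCOVA confined to the biomarkers. An analysis plan that followed this wording would carry the mismatch forward.

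**Unadjusted tests are valid, and lower power for the secondary outcomes is openly accepted.** Both are true. The accepted loss, however, is the price of Bonferroni; the loss from leaving out the baseline buys nothing.

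**The size of the gain is assumed.** It is. At r = 0.3 the gain is only about 5 percentage points, and against change scores it shrinks when r is high.

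**Logistic regression may take baseline into account.** A baseline score could be among the unnamed confounders, and the method is right for depression remission and suicidal-ideation remission. So it should not be said that logistic regression as such ignores baseline, nor that the article states it will be fitted to the BPRS or MoCA totals.

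**A mixed model could serve the two scales.** A model with baseline and end score as joint responses, and baseline means held equal between groups, is about as efficient as ANCOVA. It would be wrong to say that MMRM could not help; but section 2.8 does not assign it to these scales.

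**A stronger reading of the session data is not supported.** A reader might infer that records from successive sessions will be pooled as independent observations. Under an assumed 8 sessions and within-patient correlation 0.3 to 0.7, that would raise a nominal 5% type I error to about 27% to 42%. The document states no such analysis. A t-test on a per-patient mean, or the MMRM clause, fits the text equally well, so these figures describe no planned method.

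**Conclusion.** The point holds for BPRS and MoCA, as a loss of precision. Section 2.8 leaves them to an unadjusted comparison, names an adjusted model that does not fit a total score, and keeps the suitable one for the biomarkers. There is no bias.

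Under the assumed difference of 0.4 at 93 per group and α = 0.05/7, power moves from about 52% to between 57% and 87% as r goes from 0.3 to 0.7. The direction of the gain is certain for any r other than zero; its size rests on assumed values of d and r.

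For the per-session electroconvulsive and anaesthesia measures, only a clarification is due: the mixed-model clause is attached to no outcome. Those measures have no baseline in Table 1, so the baseline argument does not extend to them. The primary analysis, already adjusted for the stratification factors, and the 93 and 120 per group stand.

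**What to change.** Reword section 2.8:

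1. Analyse BPRS and MoCA by ANCOVA on the end-of-treatment score, with treatment, the scale's own baseline and the stratification factors as terms.
2. Limit logistic regression among the secondary outcomes to depression remission and suicidal-ideation remission, adjusted for the stratification factors in place of unnamed confounders.
3. As a clarification, tie the mixed model, or a stated per-patient summary, to the electroconvulsive and anaesthesia measures, so that sessions within a patient are not treated as independent.

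The cost is a few sentences, settled before unblinding. No new data, visits or participants are needed, and ANCOVA is already planned for the biomarkers.

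### Blood biomarkers are placed under both Bonferroni and Benjamini–Hochberg, so the secondary-outcome family, its threshold and the family-wise claim do not fit together

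*Protocol article*

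**What the plan says.** Table 1 in section 2.6 has seven rows under its secondary heading: depression remission, suicidal-ideation remission, psychotic symptoms, cognition, electroconvulsive parameters, anesthesia data and "Blood biomarkers". The text of section 2.6 that introduces the secondary outcomes names five biomarkers: AA, IL-1β, IL-6, TNF-α and BDNF.

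Section 2.8 then makes three statements on multiplicity:

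- A general rule: "the Bonferroni correction will be applied for the secondary and exploratory outcomes".
- A more specific version of it: "the Bonferroni correction will be applied uniformly across all pre-specified secondary outcomes to control the family-wise error rate". The protocol adds that it knows this is conservative and accepts the loss of power.
- A rule for the biomarkers alone. They are called exploratory, analysed by ANCOVA adjusted for baseline, and "the Benjamini–Hochberg false discovery rate (FDR) procedure will be applied to correct for multiple testing".

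The section gives neither the number of tests in the Bonferroni family nor the adjusted threshold. The overall level is two-sided 0.05.

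**The concern.** The same five variables fall under two procedures that control different error rates. As listed secondary outcomes they are in the Bonferroni family. Calling them exploratory does not release them, because the general rule covers exploratory outcomes too. An analysis plan can follow only one of the two rules, so this is a conflict in the published text and not a detail left for later.

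Two things are at stake. First, whether the biomarkers are in or out changes the divisor for every other secondary outcome, including remission, suicidal ideation, psychotic symptoms and cognition. If that is settled after results are known, the choice can follow the p-values. Second, if the biomarkers are out and have their own 5%, the statement that the family-wise error rate is controlled over all secondary outcomes is no longer true.

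**Working it through.** **The plan's own figure.** The multiplicity plan states no number that could be reproduced. The nearest design figure is the primary sample size in section 2.7. With 60% against 80%, two-sided 0.05, 85% power and pooled variance:

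n = [1.960·√(2·0.7·0.3) + 1.036·√(0.6·0.4 + 0.8·0.2)]² / 0.20² = (1.270 + 0.655)² / 0.04 ≈ 92.7, so 93 per group, and 93 / (1 − 0.225) = 120.

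This agrees with the protocol and does not depend on the present point.

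**Inputs for the check.** Overall level 0.05, two-sided (section 2.8). Seven secondary rows (Table 1). Five named biomarkers (section 2.6). Two assumptions are needed because the document is silent: one test per non-biomarker row, and a true effect that would have 80% power at an unadjusted 0.05.

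**Threshold and power by reading.** The threshold is 0.05/m. Power is Φ(2.802 − z), where 2.802 = 1.960 + 0.842 and z is the two-sided critical value at 0.05/m.

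| Reading | m | Threshold | Power |
|---|---|---|---|
| Biomarkers out | 6 | 0.0083 | 56.5% |
| Biomarkers as one row | 7 | 0.0071 | 54.4% |
| Five biomarkers counted singly | 6 + 5 = 11 | 0.0045 | 48.6% |

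A remission p-value of 0.006 would be significant at a divisor of 6 or 7, but not at 11. A biomarker p-value of 0.009 fails Bonferroni at 7 or 11. It passes Benjamini–Hochberg among five, where the smallest step is 0.05/5 = 0.01.

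**Family-wise error if the biomarkers have their own 5%.** Under the global null with independent tests, the six-test Bonferroni family makes no error with probability (1 − 0.05/6)⁶ = 0.951. Benjamini–Hochberg among the five biomarkers makes none with probability 0.95. The chance of at least one false positive over all listed secondary outcomes is 1 − 0.951 × 0.95 ≈ 0.097.

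Nor does Benjamini–Hochberg hold the family-wise rate within the biomarkers once some effects are real. In simulation (100,000 runs, independent tests) it was 7.1% with two true effects among five and 6.5% with three.

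**Holm against Bonferroni.** Average power per true effect, same simulation settings and the same effect-size assumption:

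| m | True effects | Bonferroni | Holm |
|---|---|---|---|
| 6 | 2 | 56.6% | 58.1% |
| 6 | 3 | 56.6% | 59.7% |
| 6 | 6 | 56.5% | 68.3% |
| 11 | 2 | 48.7% | 49.4% |
| 11 | 11 | 48.6% | 59.4% |

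Holm's family-wise error stayed at or below 0.05 in every scenario, and under the global null it equalled Bonferroni's.

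**The case against.** The best defence is that a specific rule displaces a general one. Section 2.8 gives the biomarkers their own model, their own reason and their own correction, and the Discussion lists among the limitations that these analyses are exploratory. On that reading there is little doubt which procedure was meant for them. The reading is plausible, but it does not save the text. The Bonferroni rule is stated to be uniform, to cover all secondary outcomes and to reach exploratory ones as well, and the biomarkers stay in the secondary block of Table 1. If the exception is granted, the claim of family-wise control over all secondary outcomes fails.

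The defence is also right that the numerical effect can be small. On whole rows the divisor moves only from 6 to 7, which costs about two points of power and changes the verdict only for p-values between 0.0071 and 0.0083. The larger shift needs the biomarkers to be counted singly.

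A reader might infer more than the documents support:

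- **A divisor as low as 4 or as high as 18.** No sentence limits the family to four clinical scales. A count of 18 comes from splitting the electroconvulsive and anesthesia rows into single variables, which an analysis plan not shown here may settle.
- **That using Bonferroni is a mistake.** It is valid, and the protocol openly accepts its cost.
- **That Holm would gain about ten points or more.** That holds only if every effect in the family is real. With few real effects the gain is about 0 to 3 points.

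**Conclusion.** The point holds as a contradiction in the text. Sections 2.6 and 2.8 put the biomarkers under two incompatible rules, and this leaves the Bonferroni divisor at 6, 7 or 11. The matching loss of power, from an assumed 80% to between about 56% and 49%, rests on that assumed effect size and on one test per non-biomarker row. The 9.7% figure rests on the global null, independent tests and a six-test Bonferroni family. The primary analysis and the sample size are untouched. The wording should be reconciled before unblinding, but nothing here threatens the trial's main conclusion. Holm is a separate and optional gain in efficiency.

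**What to change.** - In Table 1 and section 2.6, move the blood biomarkers to an exploratory category, with Benjamini–Hochberg as their only correction.
- In section 2.8, take exploratory outcomes out of the general Bonferroni sentence.
- Limit the claim of family-wise control to the remaining secondary outcomes, and state how many tests that family holds. With one test per remaining row this is six, at 0.0083 each.
- As an improvement, replace Bonferroni with Holm over that family. It has the same family-wise error rate and never rejects fewer hypotheses.

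The cost is a few sentences and one table row, dated before unblinding. The biomarkers lose their secondary status, which agrees with how section 2.8 and the Discussion already describe them. Holm has one small downside: it gives no simple matching simultaneous confidence intervals. Cutting the family to four clinical outcomes, or dropping formal tests of the electroconvulsive and anesthesia variables, is a design choice that this point does not require.

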### 2.3 Randomization

We plan to enroll 240 participants. An independent investigator, who is not otherwise involved in the trial, will generate a computer-based randomization sequence. Participants will be randomized using a stratified block randomization method, with stratification based on age, sex, and baseline 24-item Hamilton Depression Rating Scale (HAMD-24) score. A fixed block size of 4 will be used. Subjects will be assigned 1:1 (n = 120 per group) to either the ascorbic acid group (AA Group) or the placebo group (Placebo Group). Concealment of allocation will be ensured until intervention using sequentially numbered, opaque, sealed envelopes. All personnel will be blind to the treatment of the subjects throughout the trial. The research staff responsible for participant enrollment will safeguard the allocation sequence but will have no involvement in the randomization process, clinical interventions, or outcome assessments. All treating clinicians (psychiatrists, anesthesiologists, nurses), outcome assessors, participants, and their families will remain blind to group assignments during the duration of the trial. Emergency unblinding is permitted only for serious adverse events requiring intervention knowledge for clinical management, per the predefined procedure.

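### Splitting baseline HAMD-24 at the median wastes about a third of the information in the exploratory treatment-by-severity test; keep the score continuous

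*Protocol article*

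**What the plan says.** Section 2.3 describes stratified block randomisation "with stratification based on age, sex, and baseline 24-item Hamilton Depression Rating Scale (HAMD-24) score". It gives no cut-points for age or HAMD-24.

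Section 2.8 defines the primary analysis as a logistic regression "with treatment group as the independent variable and pre-specified stratification factors included as covariates, will serve as the primary analytical method", reported as an adjusted odds ratio with its 95% confidence interval. Effect modification then appears twice in the same section:

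- First: "potential interaction effects between the stratification factors (age, sex, baseline HAMD-24 score) and the treatment group will be explored within this model".
- Later, as subgroup analyses by "age (<45 and ≥45 years), sex (male and female") and "baseline HAMD-24 score (divided at the median"), carried out by "including an interaction term between the treatment group and the subgroup variable in the primary statistical model (binary logistic regression").

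The subgroup analyses are labelled exploratory, and their interaction tests carry no multiplicity correction. The median split is stated for the HAMD-24 subgroup variable only. Section 2.8 does not say whose median is meant, or whether the two mentions of a HAMD-24 interaction use the same coding.

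**The concern.** Baseline HAMD-24 is a many-valued score that every patient will have. Reducing it to above or below the median treats a patient just over the cut as equal to the most severely ill patient in the trial. If the benefit changes gradually with severity, the split test is less able to show it. Interaction tests are already weak in a trial sized for an overall effect, so the loss falls where there is little to spare.

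There is also a question of consistency. Stratified blocks need HAMD-24 categories fixed before the first patient is randomised, whereas the median of the enrolled sample is known only after the last. If that is the median intended, the article attaches two different groupings to one factor, and a reader of the results could not tell which one a reported HAMD-24 interaction refers to.

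**Working it through.** **The plan's own figures.** The article gives no number for the interaction tests. Its sample size (Section 2.7) reproduces and sets the range of N. With 60% vs 80%, two-sided α 0.05 and power 85%:

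n = [1.960·√(2·0.7·0.3) + 1.036·√(0.6·0.4 + 0.8·0.2)]² / 0.2² = (1.270 + 0.655)² / 0.04 ≈ 92.7, so 93 per group.

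93 / (1 − 0.225) = 120 per group. The relevant totals are therefore 2 × 93 = 186 evaluable and 240 enrolled.

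**Information kept by a median split.** For a linear effect, the fraction kept is the squared correlation between the score x and the indicator of being above its median.

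- Normal: covariance 1/√(2π) = 0.399 and indicator variance 0.25, so 0.399² / 0.25 = 2/π = 0.637. Loss 36%.
- Uniform: 3 × 0.25 = 0.75. Loss 25%.
- Exponential: covariance 0.5·ln 2 = 0.347, so 0.347² / 0.25 = 0.48. Loss 52%.
- Simulated: normal truncated below at −1 SD, loss about 35%; gamma with shape 3, loss about 42%.

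The article does not give the distribution of baseline HAMD-24, so 25% to 52% is an assumed range, with 36% for a roughly normal score. As a rough guide, 36% is like testing the continuous score in 0.637 × 240 ≈ 153 patients instead of 240.

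**Effect on power.** The assumed model was logit(p) = ln(0.6/0.4) + t·(0.98 + 0.8·h), where t is treatment and h is standardised HAMD-24. The value 0.98 is the planned treatment effect: ln[(0.8/0.2)/(0.6/0.4)] = ln 2.667. The interaction of 0.8 log-odds per SD is an assumption. The test is the two-sided 5% Wald test of the interaction.

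| N | Continuous | Median split |
|---|---|---|
| 240 | about 74% | about 55% |
| 186 | about 63% | about 45% |

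A separate set of 1,500 simulated trials gave 74% vs 56% and 64% vs 43%. A check with 6,000 trials under the same model gave 73% vs 53% and 61% vs 42%. With 1,500 trials the simulation error of one figure is about √(0.55·0.45/1500) = 1.3 points. All runs show a loss of about 18 to 21 points.

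**Cut-points side by side.** Section 2.3 needs a HAMD-24 cut known at randomisation. Section 2.8 names the median without a source. The two can coincide only if a fixed median from outside the trial was used for both, and the article does not say so.

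**The case against.** The strongest reply is that this is a preference about an analysis the plan already calls exploratory. A cut based only on a baseline value is pre-specified and blind to treatment and outcome, so it introduces no bias and no type I error problem. A subgroup cut need not equal the randomisation cut. The power figures rest on an assumed interaction almost as large as the whole planned treatment effect (0.8 against 0.98). They also assume that the effect is linear in severity, which favours the continuous test. With a smaller interaction neither coding would have adequate power. All of this stands, and it keeps the point minor. It does not remove the point, because the plan states the less efficient method when the better one uses data already collected.

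A reader might infer three stronger conclusions, which the article does not support:

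- **That the split damages the primary adjustment.** The median appears only in the subgroup sentence. Nothing says that the covariate in the primary model is split there.
- **That arm balance is lost in the severity subgroups.** Subgroups defined by a baseline score are balanced in expectation under randomisation. Stratifying on the same cut only reduces chance imbalance.
- **That the primary odds ratio is compromised.** If all three interactions stayed in the model with 0/1 coding, the treatment coefficient would become a reference-subgroup effect. Simulated power for it would be about 35% instead of 85% (N = 186), or 43% instead of 94% (N = 240). But Section 2.8 defines the odds ratio first, from treatment and covariates, and then says that interactions "will be explored within this model for the primary outcome". That most naturally describes an extension fitted afterwards. A clarifying sentence is worthwhile, but the text contains no error here.

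**Conclusion.** The point holds as a minor improvement to one exploratory test. Dividing baseline HAMD-24 at the median discards about 36% of the information if the score is roughly normal (25% to 52% under the other shapes tried). It costs about 18 to 21 percentage points of power at an assumed linear interaction of 0.8 log-odds per SD. The distribution, the size of the interaction and its linearity are assumptions, not figures from the article. The mismatch with the randomisation strata depends on reading the median as that of the trial sample, which is likely but not stated. The sample size, the primary test and its type I error are unaffected.

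**What to change.** In Section 2.8 or the analysis plan:

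1. Test treatment by HAMD-24, and treatment by age, with the baseline variable as a continuous term. Fit each interaction in its own extension of the primary logistic model.
2. Show subgroup estimates by the fixed randomisation strata, or keep the median split and label it as display only, naming whose median it is.
3. State in one sentence that the primary adjusted odds ratio comes from the model without interaction terms.

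The cost is wording, with no new data, and it can be settled before unblinding. The one downside is an assumption of linearity on the logit scale, which can be checked, for example by adding a curved term for the score.
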